### Active SMT protocol

Active SMT includes three procedures: (1) side-lying lumbar spine manipulation, (2) prone lumbar spine mobilisation, and (3) prone thoracic spine manipulation—all delivered with therapeutic intent. These components are chosen based on their acceptability in clinical practice and their validated placebo-control counterparts [21]. The intervention provider will deliver (1) a high-velocity, low-amplitude (HVLA) thrust to the L4–L5 or L5–S1 spinal motion segments. Side-lying lumbar spine manipulation is performed bilaterally, with the intervention provider choosing any suitable technique and with or without occurrence of the characteristic joint cavitation associated with spine manipulation. The intervention provider then delivers (2) prone lumbar mobilisation by placing the contact hand and applying downward pressure over L4–L5 or L5–S1 with the other hand guiding a manual flexion-distraction piece through three sets of five full-range oscillations. The intervention provider then delivers (3) prone thoracic manipulation by applying a HVLA thrust with therapeutic intent in a posterior-to-anterior direction at the T5–T6 or T6–T7 spinal motion segments. The proposed ‘active’ element for procedures (1) and (3) is the high-velocity, low-amplitude thrust through the target spinal motion segments (i.e. L4–L5/L5–S1 in [1] and T5–T6/T6–T7 in [3]), potentially leading to neurophysiological effects [20]. For procedure (2), the proposed ‘active’ elements are the pressure, flexion, and distraction components through the target spinal motion segments (i.e. L4–L5/L5–S1). Details on the active SMT protocol—consistent with the 12-item TIDieR checklist [22]—are found in Additional file 3B.

### Placebo-control SMT protocol

Placebo-control SMT involves three procedures: (1) control side-lying lumbar spine manipulation, (2) control prone lumbar spine mobilisation, and (3) control prone thoracic spine manipulation—all performed without therapeutic intent. The three procedures are informed by previous placebo-control validation work in RCT settings [21]. Procedure (1) is operationalised as the application of a low-velocity broad push manoeuvre to the gluteal region with an inferior-to-superior nontherapeutic line of drive [21]. Procedure (2) consists of a manual manoeuvre involving 3 sets of 10 minimal oscillations (0 to ± 2°) of the flexion-distraction piece with light touch over the lumbar spine region. Procedure (3) involves two-handed bilateral superior-to-inferior scapulae push manoeuvres [21]. Additional file 3C details the placebo-control SMT protocol [23].

### Outcomes

#### Primary outcome

Our primary outcome is participant blinding within each intervention arm immediately after an intervention session, as measured by the Bang blinding index (BI) [13, 24]. The blinding assessment question states ‘As mentioned at the beginning of the study, one of the two study interventions had unknown benefits (genuine treatment) and the other intervention was not known to be beneficial (control treatment). Which treatment do you believe you received?’. There are five response options: ‘Strongly believe I received the genuine treatment’, ‘Somewhat believe I received the genuine treatment’, ‘Somewhat believe I received the control treatment’, ‘Strongly believe I received the control treatment’, and ‘I do not know which treatment I received’. Bang BI estimates (between − 1 to + 1, with 0 suggesting ‘ideal’ blinding—random guess) can be interpreted as the proportion of correct guesses beyond chance within an intervention arm. From arm-specific estimates, a sum Bang BI can be calculated measuring the difference in proportions in the same guess (0 suggesting, for example, an equal proportion of participants believing active treatment in both arms). We deem an absolute arm-specific value score of ≤ 0.3 (i.e. − 0.3 to 0.3) as suggestive of adequate blinding [25].

#### Secondary outcomes

Our first secondary outcome is participant blinding using a second BI metric—the James BI [26]. James BI provides a measure of study-level blinding (i.e., not specific to an intervention arm). The James BI is a modification of the kappa statistic that measures disagreement beyond chance and returns a value between 0 and 1. A value of 1 is returned when all responses are ‘don’t know’ (complete blinding), 0 is returned when all responses are correct (complete unblinding), and 0.5 when responses are randomly distributed (50% correct, 50% incorrect). Secondary outcomes measured after each intervention session include the following: outcome assessor blinding (Bang and James BIs), and factors influencing perceived intervention assignment among participants and outcome assessors (thematic analysis [27], answers to the open-ended questions ‘Why do you believe you received this treatment?’, and ‘Why do you believe this participant received this treatment?’ respectively). Other outcomes are included to blind the study objective from participants and foster impartiality. These are lumbar spine range of motion (ROM, maximum active total flexion and extension), self-rated general health, satisfaction with care, pain intensity, and function. In addition, participant-reported credibility of the interventions and expectancies are measured after the second intervention session with the credibility/expectancy questionnaire (CEQ) [28]. Lastly, to complement the main study objectives and provide exploratory information for the future trial, intervention provider-reported outcomes are also collected after each session. These include intervention component delivery fidelity and quality of intervention delivery relative to the protocol. See Table 1 for the schedule of study procedures related to screening, enrolment, interventions, and assessments.

**Table 1 Tab1:** Schedule of screening, enrolment, interventions, and assessments

Trial event	Screening	Enrolment	Study visit 1		Study visit 2	
Study visit period			Pre	Post	Pre	Post
Time point—days	− 1	0	0	0	+ 2 to 14	+ 2 to 14
Enrolment						
Eligibility criteria	X					
Patient information and informed expression of interest	X					
Demographics and study entry form	X					
Informed consent in-person signature at clinic		X				
Randomisation		X				
Assessments—intervention providers						
Interventions delivered			X		X	
Intervention component fidelity				X		X
Participant tolerability				X		X
Quality of intervention delivery				X		X
Assessments—participants						
Range of motion			X	X	X	X
General health			X	X	X	X
Pain intensity			X	X	X	X
Back function			X	X	X	X
Satisfaction with care				X		X
Blinding assessment				X		X
Factors influencing beliefs about intervention assignment				X		X
Credibility/expectancy of interventions						X
Assessments—outcome assessors						
Blinding assessment				X		X
Factors influencing beliefs about intervention assignment				X		X

### Sample size consideration

A precision-based approach has been used to decide sample size using the primary outcome measure of the Bang BI estimate (i.e., width of the 95% CI) rather than statistical hypothesis testing/power given the purpose of this blinding feasibility trial [29]. We estimate the Bang BI within each intervention arm and present a 95% CI for each mean BI point estimate. For a sample size of 26 participants per arm, the 95% CI is the observed BI estimate ± 0.225 points (0.45 points width of the 95% CI) for the primary outcome measure of the arm-specific Bang BI, according to Thompson’s method, as described by Landsman and colleagues (see Equation 1 in [30]). Conservatively allowing for attrition of participants of up to 15%, we aim to recruit at least 30 participants per arm (at least 60 participants in total) for this blinding feasibility RCT.

If the minimum recruitment targets for the desired precision are met, and trial participation interest is sufficient to aim for a larger study size, we will consider enrolling and conducting the trial in up to a maximum of 50 participants per arm (100 participants in total). This additional enrolment will yield more precise and informative estimates of the primary outcome.

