### Statistical methods

Blinding analyses will be conducted using an intention-to-treat approach with the R package BI, version 1.1.0 [38, 39]. The current implementation of this package supports both Bang and James BI approaches, the presence of two intervention arms, and three intervention assignment beliefs by participants (i.e., ‘genuine’, ‘control’, and ‘do not know’). Information from the five-level blinding assessment items will be descriptively analysed and tabulated with numbers and percentages. To explore the influence of SMT experience on blinding feasibility of participants and outcome assessors, the responses from the blinding assessment will be described as counts and percentages, by levels of SMT experience. Within- and between-group changes in pain intensity and lumbar ROM will be described, although no formal statistical testing is performed given that these outcomes are collected to blind the study objective from participants and are not relevant to the blinding feasibility assessment. Factors contributing to perceptions about intervention arm assignment among participants and outcome assessors will be analysed using qualitative thematic analysis [27]. The analytical approach is informed by previous feasibility work [40]. Initially, three investigators (blinded to assigned interventions) will independently group similar responses using colour codes. Subsequently, they will develop themes through an iterative and consensus-based process.

To assess the impact of possible deviations from allocated intervention, an as-treated analysis accounting for potential lack of adherence or human errors by intervention providers will be conducted, if applicable and appropriate, to assess blinding outcomes.

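### The stated 95% CI of ±0.225 with 26 per arm is not the precision of the arm-specific Bang index; near an index of 0 the half-width is 0.27 to 0.38 if up to half answer do-not-know

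*Protocol article*

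**What the plan says.** Sample size consideration (Protocol article) bases the sample size on the width of the confidence interval and sets power aside. The plan is to "present a 95% CI for each mean BI point estimate" in each arm. The precision claim begins "For a sample size of 26 participants per arm" and puts the interval at the observed index ±0.225, restated as "0.45 points width of the 95% CI) for the primary outcome measure of the arm-specific Bang BI". Thompson's method is named as the source, with a reference to an equation in a cited paper. No value of the index and no share of do-not-know answers is attached to the figure.

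Allowing for up to 15% attrition, the target becomes at least 30 per arm. Recruitment may go up to 50 per arm, with the comment "This additional enrolment will yield more precise and informative estimates of the primary outcome".

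Primary outcome says that the index runs from −1 to +1 and "can be interpreted as the proportion of correct guesses beyond chance within an intervention arm". It takes an absolute arm-specific value of at most 0.3 as adequate blinding. Statistical methods says that the software used for the blinding analysis handles "three intervention assignment beliefs by participants": genuine, control and do not know.

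**The concern.** Thompson's method gives the sample size at which every category proportion of a multinomial lies within a chosen distance of its true value simultaneously. Its distance is on the 0 to 1 scale of a proportion. The Bang index is the correct proportion minus the incorrect proportion in the same arm, on a scale from −1 to +1. The two proportions are negatively correlated, so their difference varies more than either one. A bound for each proportion therefore does not carry over to the index.

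Precision is the only reason given for the sample size, and the purpose is to inform the blinding methods of a later trial. A reader who takes ±0.225 at face value will think the arm-specific estimates firmer than they are, and may reuse the calculation.

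**Working it through.** **Inputs.** From Sample size consideration: 26 per arm, 95% confidence, half-width 0.225, minimum 30 and maximum 50 per arm. From Primary outcome: the scale and meaning of the index, and the limit of 0.3. From Statistical methods: three belief categories. Assumed, because the article does not give it: the share of do-not-know answers (DK), shown at 0%, 20%, one third and 50%.

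**Step 1: reproduce the plan's figure.** Thompson's bound is n = max over m of z²(1 − α/(2m)) · (1/m)(1 − 1/m) / d². With α = 0.05 the constant is 1.2560 at m = 2, 1.2736 at m = 3 and 1.1697 at m = 4, so the maximum is 1.2736.
- n for d = 0.225: 1.2736 / 0.050625 = 25.16, rounded up to 26.
- d at n = 26: √(1.2736/26) = 0.221.

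The named method thus returns the stated 26. Here d is the half-width for each category proportion.

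**Step 2: the interval of the Bang index.** With BI = p_correct − p_incorrect in one arm of size n:

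Var(BI) = [p_correct + p_incorrect − BI²] / n, and half-width = 1.96 · √Var.

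At BI = 0 this is 1.96 · √((1 − DK)/n). For example, n = 26 with no do-not-know gives 1.96 · √(1/26) = 0.384, and with one third it gives 1.96 · √(0.6667/26) = 0.314.

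| n per arm | DK 0% | DK 20% | DK one third | DK 50% |
|---|---|---|---|---|
| 26 | 0.384 | 0.344 | 0.314 | 0.272 |
| 30 | 0.358 | 0.320 | 0.292 | 0.253 |
| 50 | 0.277 | 0.248 | 0.226 | 0.196 |

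Away from 0 the interval narrows slowly: at |BI| = 0.3 and n = 26 it is 0.367 (DK 0%) or 0.292 (DK one third).

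**Step 3: when ±0.225 would be right at n = 26.** Setting the half-width to 0.225 requires p_correct + p_incorrect − BI² = 26 · (0.225/1.96)² = 0.343.
- At BI = 0: DK = 1 − 0.343 = about 66%.
- With no do-not-know: |BI| = √(1 − 0.343) = about 0.81.
- With one third do-not-know: |BI| = √(0.667 − 0.343) = about 0.57.

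**Step 4: sample size for ±0.225 at BI = 0.** n = (1.96/0.225)² · (1 − DK) = 75.9, 60.7, 50.6 and 37.9, so 76, 61, 51 and 38 per arm for DK = 0%, 20%, one third and 50%.

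**Step 5: sampling behaviour at n = 26 and a true index of 0** (exact multinomial).

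| | DK 0% | DK one third |
|---|---|---|
| Estimate within 0.225 of the truth | 67% | 81% |
| Estimate outside −0.3 to 0.3 | 17% | 7% |

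With no do-not-know the index moves in steps of 1/13, which lowers the 67%; the normal approximation gives about 75%. Either value is well below 95%.

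**The case against.** **The source equation is not at hand.** True. That ±0.225 is Thompson's bound for category proportions is an inference from the named method and the match to 26. The result in Step 2 does not depend on it: the index as the article describes it, with three categories, has the variance shown.

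**The do-not-know share is assumed.** This also stands, and no single replacement figure is right. But the stated half-width fails across the range from none to one half, and the article attaches no condition to it.

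**26 is not the recruitment minimum, and the maximum nearly reaches the figure.** At least 30 per arm are to be recruited, and the first blinding assessment falls on the day of randomisation, when little attrition is expected. At 30 per arm the half-widths are 0.358 to 0.253, still above 0.225. At 50 per arm with one third do-not-know, 0.226 against 0.225 is no practical difference, and with half do-not-know the claim is met. The article's remark that more enrolment improves precision is correct.

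**The adequacy limit.** A reader might infer that, because 0.31 to 0.38 exceeds 0.3, even an observed index of 0 could not be shown to be adequate, or that the interval will usually cross ±0.3. The documents do not support this. The rule reads "We deem an absolute arm-specific value score of" at most 0.3. It applies to the value of the index and does not ask for the interval to lie inside the zone. The half-width at 26 per arm and an index of 0 also falls below 0.3 once about 39% answer do-not-know (1 − 26 · (0.3/1.96)² = 0.39).

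**Little changes in practice.** Trial status reports recruitment complete, and nothing suggests that ±0.225 would be used as the reported interval, since the index is analysed with dedicated software. The outcome, analysis and adequacy rule are untouched. That limits the remedy to wording, but it does not make the stated precision correct.

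**Conclusion.** The point holds as an error in the stated precision. At 26 per arm and an index of 0, the 95% half-width is 0.384, 0.344, 0.314 or 0.272 with 0%, 20%, one third or 50% do-not-know. The full width is therefore 0.54 to 0.77 rather than 0.45. The stated figure is right only under conditions the article does not name (Step 3). This rests on the three-category form of the index, the large-sample variance, and an index near 0, which the article itself calls ideal blinding.

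The practical consequence is limited. Since adequacy is judged on the point value, the most that can be said is that a truly blinded arm of 26 would fall outside the limit by chance about 17% of the time with no do-not-know answers and about 7% with one third. The error matters because this figure is the sole justification for the sample size.

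**What to change.** Keep the recruitment range of 30 to 50 per arm. In Sample size consideration, replace the ±0.225 claim with half-widths from the Bang variance and state the assumed do-not-know share. Possible wording: *For an arm-specific Bang index near 0, the 95% CI half-width is about 0.38, 0.34, 0.31 or 0.27 with 26 per arm when 0%, 20%, one third or 50% answer do-not-know; about 0.36, 0.32, 0.29 or 0.25 with 30 per arm; and about 0.28, 0.25, 0.23 or 0.20 with 50 per arm.*

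Alternatively, keep ±0.225 but attribute it to the single response proportions and give the precision of the index separately. It would help to add the chance that an arm with a true index of 0 falls outside the 0.3 limit (about 17% to 7% at 26 per arm, for none to one third do-not-know). No sentence about the interval crossing ±0.3 is needed.

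Since recruitment is complete, the correction belongs in the results report or a correction note. The cost is wording and a less favourable stated precision. No participants, analyses or decision rules change.

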### Randomisation

#### Allocation sequence generation

A computer-generated randomisation sequence will be generated by an independent statistician at the EBPI and used to randomly allocate participants to active or placebo-control SMT (1:1 ratio). Randomisation will be stratified by SMT experience as a patient or recipient in the past three months, and low back pain in the past four weeks (3 or greater on a 0 out of 10, NRS), and blocked with randomly varying block sizes, which will not be disclosed to ensure concealment of allocation of participants, outcome assessors, data analysts, and investigators.

### Concealment mechanism and implementation

Participants will be allocated to intervention arms through a concealed, central, web-based randomisation system via REDCap; once eligibility is determined, informed consent will be obtained, and baseline data will be entered in an electronic case report form. Intervention providers will assign participants to one of the two SMT interventions—coded ‘A’ and ‘B’—at study visit 1, immediately before delivering the intervention. They will perform randomisation in a private study treatment room with an electronic device and shield the screen from the participants’ view.

### Blinding

Per protocol, participants, outcome assessors, data analysts, and investigators will be blinded to intervention assignment after randomisation. This will be achieved through appropriate trial processes keeping intervention providers and outcome assessors in separate spaces in the study clinic and emphasising the importance of no discussion of study aspects between clinicians, restricting REDCap user right privileges, and by not breaking the code of the intervention variable until two blinded data analyses are completed. Due to the physical nature of both the active and placebo-control SMT interventions, intervention providers will not be able to be blinded to the interventions they are delivering. Yet, they will be trained not to disclose the assigned intervention, nature of the interventions, nor trial objectives to trial participants or other members of the trial team.

### Data collection and instruments

The inclusion and exclusion criteria (eligibility), patient information and informed expression of interest forms, will be completed online, prior to the first study visit. The informed consent form, study entry survey, and pre- and post-intervention assessments will be completed face to face. Trial coordinators will provide participants with a tablet or laptop with the REDCap survey [18] in the study clinic waiting area. Trial coordinators will have completed Good Clinical Practice (GCP) training prior to the start of the trial. The study entry survey includes questions on height, weight, gender, experience with SMT (in the past three months and lifetime), low back pain in the past four weeks, and average pain in the past four weeks. The following outcomes with their corresponding instruments will be captured:Range of motion of the lumbar spine: Measured by placing a measuring mobile phone at T12 with the participant standing, using the iOS application *Measure®* (iOS version 16.0.2, iPhone.® model X, Apple Inc., CA, USA) [31–33]Self-rated health: Measured with an item from the RAND 36-Item Short-Form Survey Instrument [34]Pain intensity: Measured with the NRS [35]Back function: Measured with selected items from the International Fitness Scale [36], the Cornell Musculoskeletal Discomfort Questionnaire [37], and a NRS (0 [Worst possible back function] to 10 [Best possible back function])Satisfaction with care: Measured by degree of agreement with the statement ‘I am satisfied with the treatment I received today’, with five Likert-type answers—‘Strongly agree’, ‘Agree’, ‘Uncertain’, Disagree’, and ‘Strongly disagree’Beliefs about intervention assignment: Measured with blinding questionnaires [13]—a standardised approach for blinding assessmentFactors influencing beliefs about intervention assignment: Assessed with the open-ended questions ‘Why do you believe you received this treatment?’ (participants) and ‘Why do you believe this participant received this treatment?’ (outcome assessors)Credibility/expectancy of interventions: Measured with the CEQ [28]Intervention fidelity: Assessed by asking intervention providers to record in case report forms information pertaining to participant tolerance, potential procedure alteration, and occurrence of joint cavitations immediately after intervention deliveryQuality of intervention delivery: Intervention provider-completed question ‘What number do you feel best describes the quality of the intervention delivery for this participant relative to the intervention protocol you were trained to deliver?’ with 11 possible answers on a 0 to 10 NRS

### Adverse events

All adverse events are appropriately documented and reported following the Clinical Trials Ordinance applicable to the Federal Act on Research involving Human Beings.

### Statistical methods

Blinding analyses will be conducted using an intention-to-treat approach with the R package BI, version 1.1.0 [38, 39]. The current implementation of this package supports both Bang and James BI approaches, the presence of two intervention arms, and three intervention assignment beliefs by participants (i.e., ‘genuine’, ‘control’, and ‘do not know’). Information from the five-level blinding assessment items will be descriptively analysed and tabulated with numbers and percentages. To explore the influence of SMT experience on blinding feasibility of participants and outcome assessors, the responses from the blinding assessment will be described as counts and percentages, by levels of SMT experience. Within- and between-group changes in pain intensity and lumbar ROM will be described, although no formal statistical testing is performed given that these outcomes are collected to blind the study objective from participants and are not relevant to the blinding feasibility assessment. Factors contributing to perceptions about intervention arm assignment among participants and outcome assessors will be analysed using qualitative thematic analysis [27]. The analytical approach is informed by previous feasibility work [40]. Initially, three investigators (blinded to assigned interventions) will independently group similar responses using colour codes. Subsequently, they will develop themes through an iterative and consensus-based process.

To assess the impact of possible deviations from allocated intervention, an as-treated analysis accounting for potential lack of adherence or human errors by intervention providers will be conducted, if applicable and appropriate, to assess blinding outcomes.

